**Supplementary Table S1. Patient inclusion and exclusion criteria**

| Inclusion and exclusion criteria |                                                                                                                                                                                                                                                                                                                                                                                                                                                                                                                                                                                                                                                                                                 |
|----------------------------------|-------------------------------------------------------------------------------------------------------------------------------------------------------------------------------------------------------------------------------------------------------------------------------------------------------------------------------------------------------------------------------------------------------------------------------------------------------------------------------------------------------------------------------------------------------------------------------------------------------------------------------------------------------------------------------------------------|
|                                  | Description of inclusion criteria                                                                                                                                                                                                                                                                                                                                                                                                                                                                                                                                                                                                                                                               |
|                                  | Males and females; 20–85 years of age                                                                                                                                                                                                                                                                                                                                                                                                                                                                                                                                                                                                                                                           |
|                                  | Patients who have not started opioid therapy                                                                                                                                                                                                                                                                                                                                                                                                                                                                                                                                                                                                                                                    |
|                                  | Patients who will commence opioid therapy for cancer pain                                                                                                                                                                                                                                                                                                                                                                                                                                                                                                                                                                                                                                       |
|                                  | Patients capable of oral intake                                                                                                                                                                                                                                                                                                                                                                                                                                                                                                                                                                                                                                                                 |
|                                  | Patients capable of reporting the patient reported outcomes (PRO)                                                                                                                                                                                                                                                                                                                                                                                                                                                                                                                                                                                                                               |
|                                  | Patients who are prospectively to stay in the stable pathological condition during the observation period                                                                                                                                                                                                                                                                                                                                                                                                                                                                                                                                                                                       |
|                                  | Patients who are able to provide written consent to participate in this research, follow instructions during participation, and undergo protocol-specified physical examinations and other examinations, and report their symptoms or events                                                                                                                                                                                                                                                                                                                                                                                                                                                    |
|                                  | Description of exclusion criteria                                                                                                                                                                                                                                                                                                                                                                                                                                                                                                                                                                                                                                                               |
|                                  | Patients with any contraindications listed on the package insert for magnesium oxide/naldemedine or with a history of hypersensitivity to any ingredients of them                                                                                                                                                                                                                                                                                                                                                                                                                                                                                                                               |
|                                  | Patients with a serious gastrointestinal structural anomaly (e.g: mechanical ileus), a disease that influences intestinal transit (e.g: paralytic ileus, peritoneal dissemination, peritoneal cancer, uncontrolled hyper/hypothyroidism), irritable bowel syndrome (IBS), inflammatory bowel disease (IBD, e.g: ulcerative colitis, crohn's disease), active diverticular disease, pelvic disorders that cause constipation (e.g: uterine prolapse, rectal prolapse, myoma of the uterus that influences defecation). Or, patients decided by the doctor to have serious influence on gastrointestinal function (e.g: difficulty with oral intake), even if the disease written above are cured |
|                                  | Breastfeeding women or women with possible pregnancy                                                                                                                                                                                                                                                                                                                                                                                                                                                                                                                                                                                                                                            |
|                                  | Patients who had undergone a surgery or a treatment that influences gastrointestinal function (e.g: nerve block) 28days within the enrolment day, or patients planning to take them during the observation period                                                                                                                                                                                                                                                                                                                                                                                                                                                                               |

## Supplementary Table S2. Study endpoints

### Study endpoints

---

#### Primary endpoint

- Change in JPAC-QOL from baseline at 2 weeks

#### Secondary endpoints

- Change in SBMs from baseline at 2 and 12 weeks
- Change in JPAC-QOL from baseline at 12 weeks
- Change in PAC-SYM from baseline at 2 and 12 weeks
- Change in CSS from baseline at 2 and 12 weeks
- Change in RomeIV from baseline at 2 and 12 weeks
- Change in BSFS from baseline at 2 and 12 weeks
- Change in SF-36 from baseline at 2 and 12 weeks

#### Post-hoc analysis

- Change in complete spontaneous bowel movement (CSBM)
- JPAC-QOL subscale and JPAC-SYM subscale
- Numerical rating score (NRS) for pain

Abbreviations: JPAC-QOL, Japanese version of Patient Assessment of Constipation Quality of Life; SBM, spontaneous bowel movement; PAC-SYM, Patient Assessment of Constipation-Symptoms; CSS, constipation scoring system; BSFS, Bristol Stool Form Scale; SF-36, short form-36; CSBM, complete spontaneous bowel movement.

Study protocol

Comparing the effectiveness of magnesium oxide and naldemedine in preventing opioid-induced constipation: A proof of concept, single institutional, two arm, open-label, phase II, randomized controlled trial

## 0. Summery

### 0.1 Study flowchart

This study is a proof of concept, single institutional, two arm, open-label, phase II, randomized controlled trial. Study design is as follows.

[figure not shown]

### 0.2 Study objectives

Opioids are used for cancer pain management but constipation develops in many cases (Opioid-induced constipation; OIC) and impairs patients' quality of life. Thus, OIC is a problem worth investigating. The aim of this study is to compare magnesium oxide to naldemedine and investigate which is more effective in preventing OIC.

### 0.3 Eligibility

#### Inclusion Criteria:

1. Patients who received adequate explanation about this study and provided written informed consent
2. Patients who are  $\geq 20$  and  $< 85$  years of age at the time of informed consent
3. Patients who have not started opioid therapy
4. Patients who are scheduled to commence opioid therapy for cancer pain
5. Patients capable of oral intake
6. Patients capable of reporting the patient reported outcomes (PRO)
7. Patients who are prospected to stay in the stable pathological condition during the observation period

#### Exclusion Criteria:

1. Patients with any contraindications listed on the package insert for magnesium oxide/naldemedine or with a history of hypersensitivity to any ingredients of these medicine
2. Patients with a serious gastrointestinal structural anomaly (e.g: mechanical ileus), a disease that influences intestinal transit (e.g: paralytic ileus, peritoneal dissemination, peritoneal cancer, uncontrolled hyper/hypothyroidism), irritable bowel syndrome (IBS), inflammatory bowel disease (IBD, e.g: ulcerative colitis, crohn's disease), active diverticular disease, pelvic disorders that cause constipation (e.g: uterine prolapse, rectal prolapse, myoma of the uterus that influences defecation). Or, patients decided by the doctor to have serious influence on gastrointestinal function (e.g: difficulty with oral intake), even if the disease written above are cured
3. Breastfeeding women or women with possible pregnancy
4. Patients who had undergone a surgery or a treatment that influences gastrointestinal function (e.g: nerve block) 28days within the enrolment day, or patients planning to take them during the observation period

#### 0.4 Planned number of subjects and study period

Planned number of subjects: 120 subjects (60 for each group)

Study period: From March 22, 2018 to March 31, 2023

#### 0.5 Study method

The study consists of a screening period for 4 weeks and a treatment period for 12 weeks. Cancer patients scheduled to commence opioid therapy will be randomly

allocated into magnesium oxide (500mg (1 tablet), thrice daily after each meal) or naldemedine (0.2 mg/day (1 tablet), once daily after breakfast) groups and will orally administer each study drug for 12 weeks during the treatment period.

The primary endpoint will be the change in the Japanese version of The Patient Assessment of Constipation Quality of Life (JPAC-QOL) from baseline at 2 weeks. The Patient Assessment of Constipation Symptoms (PAC-SYM), the Constipation Scoring System (CSS), the Bristol Stool Form Scale will also be examined. The presence of constipation will be assessed before and after drug administration using the Rome IV criteria.

### **1. Objectives and background of the study**

Opioids are used for cancer pain management [1,2]; however, there are challenges associated with continuous opioid therapy owing to complications such as nausea, constipation, sleepiness, and respiratory depression [3-6]. Constipation develops in 15-64% of patients receiving strong opioid analgesics [7-11]. Long duration of opioid therapy is greatly responsible for opioid-induced constipation (OIC) [12] and drug tolerance against OIC is barely made, so preventive administration of laxatives is important [13].

Over the years, little progress has been made in OIC treatment research [9]. Conventional OIC treatment involves a “non-drug” therapy comprising the consumption of high fiber diets or medications like laxatives, but neither of them targets the underlying mechanism of OIC [3,9]. OIC occurs when opioids act on  $\mu$ -receptors in the intestinal nerves, reducing intestinal motility and intestinal fluid secretion [6,14]. Recently, peripherally acting  $\mu$ -opioid receptor antagonists (PAMORAs), such as naldemedine, were shown to treat OIC. Naldemedine is a novel PAMORA being developed for the treatment of OIC without affecting central analgesia [15] and safety and efficacy of it has been reported to be superior to that of placebos [16,17].

Symptoms brought by constipation (abdominal pain, abdominal fullness, loss of appetite) impairs patients' QOL, hence the need for preventive treatment. This study will compare magnesium oxide to naldemedine and investigate which is more effective in preventing OIC.

## **2. Scientific rationale for the study**

### **2.1 Study Diseases**

New, or worsening, symptoms of constipation when initiating, changing or increasing opioid therapy, that must include 2 or more of the following > 25% of the time;

- Lumpy/hard stools
- Sensation of incomplete evacuation
- Sensation of anorectal obstruction/blockage
- Manual maneuvers to facilitate defecations
- Reduced stool frequency (fewer than 3 spontaneous bowel movements per week)

### **2.2 Current state of treatment**

Current OIC treatments include non-drug and drug therapies. Non-drug therapies include abdominal massage and high-fiber diets. For drug treatment, osmotic laxatives are the first choice according to the Palliative Medicine Society's guidelines in Japan and the use of chloride channel activators (lubiprostone) and stimulant laxatives (e.g. senna) is also recommended [11]. For the prevention of OIC, the Society for Palliative Medicine recommends prophylactic administration of magnesium oxide or naldemedine.

### **2.3 Study Method/Design**

This study is an investigator-initiated, single-center, open-label, two-arm, randomized controlled trial. Cancer patients scheduled to commence opioid therapy will be randomly allocated into magnesium oxide (500mg thrice daily) or naldemedine (0.2mg once daily) groups and take each drug for 12 weeks. The endpoints will be the PAC-QOL, PAC-SYM, CSS, Roma IV and Bristol Stool Form Scale.

## **3. Study drugs**

Naldemedine, Magnesium oxide

## **4. Diagnostic criteria of the disease**

New, or worsening, symptoms of constipation when initiating, changing or increasing opioid therapy, that must include 2 or more of the following > 25% of the time;

- Lumpy/hard stools
- Sensation of incomplete evacuation
- Sensation of anorectal obstruction/blockage
- Manual maneuvers to facilitate defecations

- Reduced stool frequency (fewer than 3 spontaneous bowel movements per week)

## **5. Eligibility**

Patients with cancer who meet all the following inclusion criteria and do not meet any of the exclusion criteria will be included in this study.

### **5.1 Inclusion Criteria**

1. Patients who received adequate explanation about this study and provided written informed consent
2. Patients who are  $\geq 20$  and  $< 85$  years of age at the time of informed consent
3. Patients who have not started opioid therapy
4. Patients who are scheduled to commence opioid therapy for cancer pain
5. Patients capable of oral intake
6. Patients capable of reporting the patient reported outcomes (PRO)
7. Patients who are prospectively to stay in the stable pathological condition during the observation period

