## 10. Study endpoints

### 10.1 Primary Endpoint

The change in JPAC-QOL from baseline at 2 weeks

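### The primary comparison pools patients with and without constipation before any opioid, so its mean change mixes relief of existing constipation with prevention of OIC; baseline Rome IV status should enter the model and the reporting.

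*Protocol*

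**What the plan says.** - **Aim.** Section 0.2: "The aim of this study is to compare magnesium oxide to naldemedine and investigate which is more effective in preventing OIC". Section 1 repeats it.
- **Definition.** Sections 2.1 and 4 define OIC as "New, or worsening, symptoms of constipation when initiating, changing or increasing opioid therapy", with at least two listed symptoms.
- **Entry.** Section 5.1 takes "Patients who have not started opioid therapy" and "Patients who are scheduled to commence opioid therapy for cancer pain". Section 5.2 removes certain causes of constipation (structural and transit disease, IBS, IBD, diverticular disease, pelvic disorders). Neither section has a criterion on constipation as such.
- **Measurement.** Section 0.5: "The presence of constipation will be assessed before and after drug administration using the Rome IV criteria". The schedule in Section 9.3 includes Rome IV at baseline, and Section 10.2.1 lists change in Rome IV as a secondary endpoint.
- **Randomisation.** Section 6.4 stratifies by age and gender only.
- **Primary endpoint and test.** Section 10.1: "The change in JPAC-QOL from baseline at 2 weeks". Section 11.2 compares the two groups by one-way ANOVA with a Student's t-test in the full analysis set. No covariate is named.

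**The concern.** A patient who has not yet taken an opioid cannot have OIC as Section 4 defines it, so constipation present at entry has another cause. If that patient's JPAC-QOL score falls below its pre-opioid level, at least part of the fall is relief of the earlier condition. In a patient without constipation at entry, successful prevention shows as little or no worsening. The primary mean change averages the two in proportions that the trial neither fixes nor reports.

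The relative effect of the drugs could differ between the two kinds of patient. Section 1 says "OIC occurs when opioids act on" receptors in the intestinal nerves, presents naldemedine as an antagonist at such receptors, and says that conventional treatment does not target that mechanism. A difference in the pooled mean could thus come mainly from either group and still be reported as a result about prevention.

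**Working it through.** **1. The text.** Three facts together give the mixing: the aim is prevention of OIC (0.2, 1); entry is open whether or not the patient is constipated (5.1, 5.2); and the endpoint is change from a pre-opioid baseline, analysed without regard to constipation status (10.1, 11.2). The ban in Section 7.4.1 on regular use of other laxatives narrows the constipated group, but does not keep out a patient with untreated constipation.

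**2. The plan's own figure.** Section 11.1 gives mean changes of -1.19 and -0.76 (difference 0.43), SD 0.76, two-sided 5%, and 51 per arm for 90% power. With a two-sample t-test, standardised difference 0.43/0.76 = 0.566:
- 51 per arm gives 80.8% power;
- 60 per arm gives 86.7%;
- 90% needs 67 per arm.

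The stated 51 does not reproduce at 90%. That is a separate matter. Below I use the planned 60 per arm, with 86.7% as reference.

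The planning changes come from 10 patients who already had OIC. Mean falls of 0.76 to 1.19 presuppose impaired quality of life at baseline, so they describe treatment more than prevention.

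**3. Effect on the pooled difference.** Let p be the share constipated at baseline (assumed; the Protocol gives none). Suppose the drugs differ by 0.43 in patients without constipation and by 0.43x in the others. Then

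pooled difference = 0.43 × [(1 - p) + p·x].

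| p | x = 0: difference | power, 60 per arm | x = 0.5: difference | power, 60 per arm |
|---|---|---|---|---|
| 20% | 0.344 | 69% | 0.387 | 79% |
| 40% | 0.258 | 45% | 0.344 | 69% |
| 60% | 0.172 | 23% | 0.301 | 58% |

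In the reverse case (0.43 only in constipated patients, none in the others), the pooled difference is 0.43p. For p = 40% to 60% that is 0.172 to 0.258, with no preventive difference at all. The pooled result cannot tell these cases apart. The table shows how much the answer depends on p and x. It does not predict what will happen.

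**4. Effect on precision.** Even with the same 0.43 in both groups, different mean changes widen the unadjusted SD. Take 0.76 as the SD within each group and assume mean changes of -0.975 (the average of -1.19 and -0.76) in constipated patients and 0 in the others:

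SD = √[0.76² + p(1 - p) × 0.975²].

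- p = 25%: SD 0.869, power at 60 per arm 77%.
- p = 50%: SD 0.903, power 74%.

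With baseline status in the model, the residual SD returns to 0.76 and power to about 87%.

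**5. What the separate estimates can bear.** With p = 40%, each arm has 60 × 0.6 = 36 patients free of constipation.
- Power for 0.43 in that group: 66%. Standard error 0.76 × √(2/36) = 0.179, so the 95% interval is about ±0.35.
- Interaction: 24 constipated and 36 other patients per arm give a standard error of 0.76 × √(2/24 + 2/36) = 0.283. Power for an interaction as large as 0.43 is about 33%.

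These analyses can inform the reading of the result. They cannot serve as a gate.

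**The case against.** Several points on the other side stand.

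- **The definition covers worsening.** A patient already constipated can still develop OIC, so admitting such patients is consistent with the aim. A reader might infer that eligibility contradicts the objective, or that every fall in a constipated patient is treatment only. The documents support neither: such a fall can combine relief with prevented worsening. What remains is that one mean cannot separate the two.
- **There is no bias between arms.** Allocation is 1:1 and randomised, so baseline constipation is balanced in expectation. The pooled difference validly compares the drugs in patients starting opioids.
- **Rome IV is used.** A reader might infer that the baseline result is collected and then ignored, but it feeds a secondary endpoint (10.2.1). What Section 11.2 lacks is its use in the primary comparison.
- **The large power losses are conjecture.** A fall to 23% assumes a 60% share and no difference at all in constipated patients, who also receive opioids. It also assigns the 0.43 to patients unlike those in whom it was seen. That the two effects might cancel is likewise unsupported: the Protocol gives no result by prior constipation.
- **An analysis plan might add subgroups.** It might, so their absence alone would be no finding. But Section 11.2 itself states the unadjusted primary test, and the link between aim and endpoint is set in the Protocol.

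**Conclusion.** The point holds as one of interpretation and possible loss of precision. The pooled change in JPAC-QOL is a valid measure of the drugs' relative effect on constipation-related quality of life in patients starting opioids. It is not, on its own, a measure of prevention of OIC. The Protocol should not go straight from the one to the other.

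The size cannot be fixed from the documents. It depends on the share constipated at baseline, the treatment difference in each group and the gap between their mean changes, none of which is given. The figures above rest on assumed values and on planning inputs from 10 patients with established OIC. This is a worthwhile improvement, not a flaw that invalidates the trial.

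**What to change.** In Section 11.2:

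1. Replace the unadjusted primary test with a linear model for the change in JPAC-QOL at 2 weeks, with treatment and baseline Rome IV constipation status (yes/no). State which criteria define that status before the opioid, since the definition in Section 4 is tied to starting, changing or increasing opioid therapy.
2. Pre-specify that the treatment difference with its confidence interval is also reported separately for patients with and without constipation at baseline, with the interaction as a supportive, descriptive analysis.
3. Describe the pooled result as the effect on constipation-related quality of life in patients starting opioids. Interpret prevention in light of the patients free of constipation at baseline, without making significance in that subgroup a condition.

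Eligibility, stratification, visits and data collection stay as they are. The cost is wording, one model term and subgroup estimates that must be read with care: at an assumed 40% share, 36 patients per arm and about 66% power for the planned difference.
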